### Recruitment strategies

#### Recruitment of PCNs

Participating PCNs will have signed a collaboration agreement (convenience sampling). The role of PCNs in the study, as explained in Table 2, is to facilitate the local coordination of the project, (1) by bringing the research team in contact with local GP circles and local GPs interested in palliative care (research), (2) by organizing educational sessions for GPs and paramedics and (3) by supporting the logistics of both the quantitative and qualitative data collection.

Participating PCN are paid a small financial compensation for completion of these tasks.

#### Recruitment of GPs through educational sessions

A diversity of educational sessions is organized to inform local GPs (and local paramedics) within the territories of participating PCNs. A kick-off workshop is organized at the start of the intervention in every region (see Table 2). In this kick-off workshop, GPs and paramedics are invited to attend a 3-hours program discussing the highlights of the CPPPC (see 1.4). This kick-off workshop aiming for an audience of 50 to 100 participants is designed to help ‘spreading the news’ to all local primary health care professionals. This rather large-scale recruitment intervention is followed by many interventions of a smaller scale: Continued Medical Education sessions for GPs for 10 to 50 participants during 1 to 1,5 hours and GP office visits for mostly 1 to 10 GPs during 30 to 60 minutes. These small-scale educational sessions are ideal to have (group) discussions on the barriers and facilitators to deliver palliative care in general and to promote the CPPPC as a tool to improve palliative care practices.

GPs showing interest in the project, by attending these educational sessions about the CPPPC, are asked to participate in the study (convenience sampling). Participating GPs will have signed a collaboration agreement and will know that for the first questionnaire filled and for patients included for the project (see 2.6.1) they will be paid a small compensation fee.

#### Recruitment of patients and informal care givers

Participating GPs have received minimal training on informed consent taking for research purposes by the research team and are asked to include eligible patients (see 2.3) for follow-up of the intervention. GPs are taught about the importance of having the support of the patients’ informal care givers for the completion of the surveys. Therefore every patient is asked to appoint a relative for assistance. Patients are asked by their own GPs to sign the informed consent form. Patients and their informal care givers will not be rewarded financially for their participation.

### Linkage of health care consumption data and questionnaire data

Both data collection systems (questionnaires from GPs and people in the palliative care setting besides health care consumption data) will be linked securely allowing more in-depth analysis, taking into consideration all confidentiality regulations, as promulgated by the National Commission for the Protection of Privacy and its Sectorial Committee of Social Security and Health Care. Therefore, the Sectorial Committee had to give written approval in advance with all data handling procedures as used in this research project. (deliberation number SCSZG/13/251 dd. 19 November 2013) The acronyms used in this chapter refer to the figures showing the data linkage process.

#### Coding procedure for the health care consumption data: standard data trajectory of the IMA (see Fig. 2)

**Fig. 2 Fig2:**
[figure not shown]
Coding and encryption: standard data trajectory of the IMA

First, at the level of the HI funds, the unique NN of all patients in the study population (see 2.3) will be transformed by the security officer to the patient-pseudo code C1. This C1 still is linked to the original health consumption data and will be sent to the Trusted Third Party (TTP) of the respective HI funds, which encrypts the data (####) while transforming C1 to another pseudo code C2. In the end, these encrypted data (###) paired with the C2 pseudo code are sent to the Data Ware House of the IMA. Here, all encrypted health care consumption data are stored in a secured way. This is the standard data trajectory of the IMA.

#### Selection of relevant health care consumption data for the prospective study

The TTP of the HI funds knows which C2 of the IMA-Data Ware House is linked to which C1. This is how the relevant IMA data (see 2.5 for more details) can be extracted by the TTP of the HI funds and stored in a separate sector of the IMA Data Ware House: the Project Data Ware House.

The IMA analyst will now categorize IMA-data and label the desired groups of GPs and patients(see 2.10 for more details). For this procedure, the IMA analyst works with research data linked to the unique project code and with the original NIHDI-number of the GPs of the research clusters. The original NIHDI-numbers are only coded in a later stage of the coding and linkage procedure because the original NIHDI-numbers are needed by the IMA-analyst to perform the pre-analysis.

#### Coding procedure for the questionnaire data (see Fig. 3)

**Fig. 3 Fig3:**
[figure not shown]
Data flow of patients having signed an informed consent (questionnaires available)

All data from the questionnaires (Qdata) initially are linked with the personal NN of patients. For GPs, the data are linked with their NIHDI number. Immediately after answering, this privacy-sensitive information is sent directly to eHealth, which will perform three actions.

First, a unique Project Random Number (PRN) to be used only in this specific data handling procedure is linked with the NN. The link between these two numbers will be sent to the security officers of the different HI funds. Here again, the unique NN will be transformed towards a patient pseudo code C1 and then sent to the Trusted Third party (TTP) of the HI funds.

Secondly, eHealth sends the link between the PRN and the project code, i.e. the patient-pseudo code which will ultimately be used for analysis (Cproj), to the TTP of the HI funds.

Finally, a third link between the project code (Cproj) and the questionnaire data (Qdata) is sent from eHealth to the TTP of the HI funds.

#### Linkage of questionnaire data and health care consumption data (see Fig. 3)

After pre-analysis, the IMA project database (Idata) is sent through the TTP of the HI funds to the authors’ Data Ware House which will be used to analyze all completely coded data, whether they come from the questionnaires (Qdata) or from the IMA (Idata). At this last stage, the original patient’s NNs are replaced by project codes (Cproj) and the doctor’s original NIHDI-numbers are replaced by doctor pseudo codes (Cdoct). Survey and IMA data will be linked with an estimated failure risk of max. 2-3 %.

#### Selection of relevant health care consumption data for the retrospective study (see Fig. 4)

**Fig. 4 Fig4:**
[figure not shown]
Data flow of patients not having signed an informed consent (surveys not available)

For patients not having signed an informed consent, the inclusion and first data flows are different and questionnaire data are off course not available. The inclusion will be done in the database of the HI funds as explained in “2.3 Study population”.

Of these people, the NN will be sent to the security officers of the HI funds. These officers will send the NN to eHealth. From then on, the data flow is very similar to the one of patients with an informed consent.

### Analysis

For the analysis of primary and secondary outcome measures, longitudinal and cluster analysis are to be used to compare data of patient populations of participating GPs vs. patient populations of non-participating GPs. If possible, the IMA will match included GPs with control GPs based on age category (per 5 years) and GP circle. If matching proves not to be realistically achievable, these characteristics of the GPs will be considered independent variables.

The data related to monitoring the implementation of the CPPPC and the quality of care and quality of life, are to be used descriptively to contextualize the primary and secondary outcomes related to participating GPs and patients. To be able to describe the GPs’ patient populations, data will also be available through the IMA on the patients’ age category, gender, month of death, disease category (cancer vs. non-cancer; presence of dementia) and socio-economic status.

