### Stepped wedge cluster procedure

It was decided to have phase intervals of six months, starting from the 1st of April 2013. The first phase is a ‘usual care’ phase for all the clusters. Every next phase, the intervention will be started in one cluster. The last intervention phase (phase 6) lasts until the 31st of March 2016. After this last date, no more ‘interventions’ on behalf of the study will be undertaken: neither meetings or educational sessions or recruitment of GPs and patients for the study.

A post-intervention data collection period for included patients will follow. This period (phase 7) lasts for 33 months, enabling the authors to cope with the effect delay of the intervention: patients will probably not all die in the same phase they were included in the study. Data collection will stop the 31st of December 2018.

A time schedule of the ‘stepped wedge cluster design’ is shown below (Fig. 1).

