### Study population

A comparison will be made between the patient populations of participating and non-participating individual GPs, located within the territories of the participating PCNs(see 2.5). Data of participating patients will be used to monitor level of implementation and quality of care (see 2.6).

Patients of which data will be available correspond to these criteria:To have a GP residing within the territory of a participating PCN, or to be domiciled there if the patient does not have a GP;To have died a ‘non-sudden death’ in the study period (data of patients for comparison of GPs’ patient populations) and/or have a ‘positive surprise question’ according to their GP [20] (data of participating patients for the monitoring of quality of care);To be at least 45 years old at the moment of inclusion.

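### The primary comparison of volunteer with non-volunteer GPs is not tied to the usual-care period, so a volunteer difference may be read as an effect of the care pathway

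*Protocol article*

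**What the plan says.** The protocol article describes the primary comparison in three places, each time by participation status. The abstract (Methods/Design) and Study population set patients of GPs who take part against patients of GPs who do not. In Study population the words are: "A comparison will be made between the patient populations of participating and non-participating individual GPs". Under Analysis, "longitudinal and cluster analysis are to be used to compare data of patient populations of participating GPs vs. patient populations of non-participating GPs".

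Participation is voluntary. In Recruitment of GPs through educational sessions: "GPs showing interest in the project, by attending these educational sessions about the CPPPC, are asked to participate in the study (convenience sampling". The order of the regions is not randomised either, which the article states openly.

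Two steps are planned against imbalance between GPs. The first is matching: "If possible, the IMA will match included GPs with control GPs based on age category (per 5 years) and GP circle". If matching fails, "these characteristics of the GPs will be considered independent variables". Patient age, sex, disease category and socio-economic status will also be available, but are mentioned for describing the populations.

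The design has a usual-care period. Phase 1 is usual care in all five clusters. After that, "Every next phase, the intervention will be started in one cluster". The Sample size calculation uses this: it expects pre-existing differences between GPs' patient populations, powers a contrast of trained with untrained GPs, and lowers the number of GPs from about 440 to about 180 because of five steps and one baseline measurement.

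**The concern.** GPs who attend palliative care sessions and then volunteer may already have fewer hospital deaths among their patients. Interest in palliative care is a likely reason for volunteering, and neither GP age nor GP circle measures it. With neither GPs nor regions randomised, the main protection in this design is the comparison of each group with its own usual-care period. The Analysis section does not say that the comparison is built on that period.

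The sample size and the analysis also describe different contrasts. A participating GP is untrained until the start, so trained versus untrained changes over time, while participating versus non-participating does not. Two readings of the Analysis section follow:

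- Only deaths after the start are compared. A pre-existing volunteer gap then goes straight into the estimated effect.
- All deaths of participating GPs count as participating, including those before the start. A true effect is then diluted.

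These are alternatives and cannot both apply. In either case it would be hard to attribute the result for the primary outcome to the pathway.

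**Working it through.** **Inputs.** From the Sample size calculation: ICC 0.2, 9 eligible deaths per GP, 180 participating GPs, about 3500 GPs in all (so 3500 − 180 = 3320 others), 80% power. From Primary outcome: 50% to 35% hospital deaths. From Stepped wedge cluster procedure: six phases of six months, then phase 7 of 33 months. Assumed: two-sided 5% level, and the size of any volunteer gap.

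**1. The plan's own figures.** For 50% versus 35%, the usual formula gives 170 patients per arm. The cluster design effect is 1 + (9 − 1) × 0.2 = 2.6, and 170 × 2.6 = 442. The article cites its stepped-wedge formula without printing it. A standard design effect with 5 steps, 1 baseline, 1 measurement per step and n = 9 is

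[1 + 0.2(45 + 9 − 1)] / [1 + 0.2(22.5 + 9 − 1)] × 3(0.8) / [2(5 − 1/5)] = (11.6 / 7.1) × 0.25 = 0.408.

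Then 442 × 0.408 = 180.5. The numerals 440 and 180 are reproduced, though here as patients per arm rather than GPs. That labelling is a separate matter, and the 180 GPs are taken as stated below. For this point, what matters is that the reduction comes from a factor that relies on comparing clusters before and after their start.

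**2. Volunteer gap with no true effect, pre-start deaths not used.** For *a* participating and *c* control GPs:

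SE = √[2.6 × 0.25 × (1/(9a) + 1/(9c))]

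- *a* = *c* = 180 (one matched control each): √[0.65 × 2/1620] = 2.83 points.
- *a* = 180, *c* = 3320 (all others): √[0.65 × (1/1620 + 1/29880)] = 2.06 points.

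P(significant) = Φ(gap/SE − 1.96) + Φ(−gap/SE − 1.96):

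| Assumed gap | 180 v 180 | 180 v 3320 |
|---|---|---|
| 0 | 5% | 5% |
| 3 points | 19% | 31% |
| 5 points | 42% | 68% |

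**3. The alternative reading: pre-start deaths pooled as participating.** Pre-start region-phases in phases 1 to 6 number 5 + 4 + 3 + 2 + 1 + 0 = 15 of 30. With equal deaths per region-phase and every GP starting with the region, a true 15 points would show as 15 × 15/30 = 7.5. Phase 7 adds 5 × 33/6 = 27.5 exposed region-phases. Then (15 + 27.5)/(30 + 27.5) = 0.739, and 15 × 0.739 = 11.1 points. GPs who join later than their region have more pre-start time, so the dilution would be larger.

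**4. Precision with pre-start deaths.** Take one pre-start phase (9/2 = 4.5 deaths per GP), 9 later deaths per GP, and a GP effect constant over time. Within-GP variance is 0.25 × 0.8 = 0.20.

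SE = √[0.20 × (1/4.5 + 1/9) × (1/180 + 1/180)] = 2.72 points.

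Against 3320 controls it is 1.98 points. Power for 15 points exceeds 99% in both cases. With the same later deaths, the simple contrast had SEs of 2.83 and 2.06, so using the pre-start deaths costs no needed power.

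**The case against.** A reader might infer that the plan leaves each GP's pre-start deaths out of the primary analysis. The article does not support that. The sentence opens with "longitudinal and cluster analysis are to be used", phase 1 is usual care everywhere, health care consumption data cover all deaths in the study period, month of death is available, and the sample size counts a baseline measurement. No section excludes pre-start deaths. Nor can it be said that volunteer differences will be taken for an effect, since partial control by GP age and circle is planned. The pooled reading also sits badly with the trained-versus-untrained contrast in the Sample size calculation.

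Model details such as the link function, random effects and coding of exposure belong in an analysis plan that is not shown, and their absence from an article is no fault.

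This narrows the point without removing it. Longitudinal names a family of methods, while the stated object is still to "compare data of patient populations of participating GPs vs. patient populations of non-participating GPs". A repeated-measures comparison of volunteers with non-volunteers on post-start deaths alone would comply fully with the section and could be confounded by volunteering.

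Two cautions on the remedy also stand. Adding the GP's pre-start hospital death rate to the matching is unwise, because about 4.5 deaths in a six-month phase make that rate too noisy and invite regression to the mean. And the change goes beyond wording: data collection runs to 31 December 2018, and the article does not say that GP start dates reach the linked data.

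**Conclusion.** The point holds in a limited form. The article fixes the primary contrast by participation status, among self-selected GPs, with two GP characteristics as the only named controls. It does not tie that contrast to the usual-care period on which its sample size depends. A volunteer difference may therefore be mistaken for an intervention effect or, on the other reading, a true effect may be diluted.

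The sizes are illustrations. The rates of 19% to 31% (3-point gap) and 42% to 68% (5-point gap) rest on assumed gaps, no true effect, 9 deaths per GP, an ICC of 0.2, a two-sided 5% level, and matching or adjustment that leaves the gap untouched. The article reports no gap. The fall from 15 to 7.5 points (11.1 with phase 7) applies only if pre-start deaths are pooled, with GPs starting when their region does.

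**What to change.** In the Analysis section, define the primary effect as a difference-in-differences. The model should contain:

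- a term for GPs who ever participate;
- effects for region and calendar phase;
- a random effect for GP;
- an exposure indicator equal to 1 only for participating GPs' deaths after the start, and 0 otherwise.

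Fix in advance whether the start is the region's or the GP's own. The region's date is known from the design, but counts late joiners as exposed before they join. The GP's date is closer to actual exposure, but must be recorded. Report the pre-start difference in hospital death rate between the groups beside the primary result. Keep the planned matching or adjustment on age and circle, and do not match on the GP's pre-start rate.

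The cost is modest extra analysis and, if the GP's own start is used, carrying that date into the linked data. The remaining weakness should be stated: only volunteer differences that stay constant over time are removed.

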## Methods/Design

### The stepped wedge cluster design (quasi-experimental)

For this study, a cluster design with a “stepped wedge” approach was chosen. This type of trial design involves sequential roll-out of an intervention to clusters over a number of time periods. The order in which clusters start the intervention is determined at random. In the end, all clusters will have started the intervention. This trial design is particularly interesting 1) when a certain intervention cannot be started simultaneously in all clusters, for instance because of logistical or financial reasons and 2) when researchers want to prevent ethical objections arising from withholding an intervention anticipated to be beneficial [29].

Five clusters will be involved (Table 3). The implementation of the CPPPC will be initiated in all clusters, in a stepped way. Ideally, to reduce bias, the different clusters need to be randomized from the start of the project. However, in this particular study, it was impossible to randomize the order of the regions from the beginning. Not all 5 clusters were well defined at the start of the project. Whenever we found a region’s palliative care network ready to participate, we offered that region the choice to start in the next phase, regardless of any preferences as a research team. That is why this study should be called a quasi-experimental study based on a stepped wedge cluster design.

**Table 3 Tab3:** Characteristics of the five participating clusters, in chronological order of planned start [.]

Cluster	Official language	Nr of inhabitants [46]	PCN/Palliative home care teams situation	GP circles
1: Zone of Antwerp	Dutch	765.470	One legal entity	12, of which 3 not completely in the territory
2: Zone of Mons	French	572.979	One legal entity	8, of 3 which not completely in the territory
3: Brussels Capital Region	Dutch/French	1.163.486	1 PCN, 1 Dutch-speaking and 3 French-speaking palliative home care teams	1 Dutch-speaking + union of 19 French-speaking
4: Province of Limburg	Dutch	856.280	PCN and palliative home care teams separate, residing in the same building	17, of which 1 not completely in the territory
5: Province of Namur	French	484.737	One legal entity	8, of which 2 not completely in the territory

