### Sample size calculation

The average size of the patient population per active GP is estimated to be approximately 1000 [15]. With a mortality of 1 % per year [38], 10 patients per GP per year are expected to die, of which 9 are expected to die non-suddenly [39]. Pre-existing differences are expected to exist between the patient populations of GPs. For instance (although not found in literature), the age of GPs is expected to be positively correlated with the age of his patients, which is relevant for palliative care delivery. On a district level, the availability of health care services [40] and on a socio-cultural level the preferred use of health care services also influence patient outcomes [41]. Therefore, we assume in the following power calculations a relatedness between eligible patients within a GP patient population expressed by an intra-class correlation coefficient of 0.2 and an average of 9 eligible patients per GP.

To detect a difference of 15 % hospital death rate between the trained and the untrained GPs, a classic randomized control trial with two groups, taking into account an intra-class correlation coefficient of 0.2, would require a sample size about 440 GPs to reach 80 % statistical power. Thanks to the stepped wedge design implemented in this study, with 5 clusters, 5 steps and 1 baseline measurement, the required sample size of GPs is reduced to approximately 180, as calculated in a recently published formula [42]. The total number of GPs amenable in this study is approximately 3500. Hence, a participation rate of 5 % is required. This participation rate of 5 % is considered realistically achievable, according to Rogers’ Innovation/Adoption curve (15 % of all people are considered ‘innovators’ and ‘early adaptors’, adapting innovations fast) [43].

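### For a comparison of volunteer with non-participating GPs, the plan names only GP age and GP circle as control variables and gives the available patient case-mix data only a descriptive purpose

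*Protocol article*

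**What the plan says.** The Analysis section of the protocol article defines the contrast: "longitudinal and cluster analysis are to be used to compare data of patient populations of participating GPs vs. patient populations of non-participating GPs". It then names how the groups will be made comparable. If possible, "the IMA will match included GPs with control GPs based on age category (per 5 years) and GP circle". The fallback uses the same two variables: "If matching proves not to be realistically achievable, these characteristics of the GPs will be considered independent variables".

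The next paragraph introduces the patient-level variables with a single purpose: "To be able to describe the GPs’ patient populations, data will also be available through the IMA". The list covers age category, gender, month of death, "disease category (cancer vs. non-cancer; presence of dementia) and socio-economic status".

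The groups are not formed by chance. On region order, the stepped wedge section says "it was impossible to randomize the order of the regions from the beginning". GPs who show interest by attending educational sessions on the care pathway "are asked to participate in the study (convenience sampling").

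The Sample size calculation section expects pre-existing differences between GPs' patient populations. As an example it says that "the age of GPs is expected to be positively correlated with the age of his patients", notes that this was not found in the literature, and calls it relevant for palliative care delivery.

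**The concern.** The primary outcome is place of death, compared between groups formed by volunteering. If patients of participating GPs differ from the others in age, diagnosis, dementia or social position, and these characteristics are related to dying in hospital, the difference in mix enters the comparison. The plan expects such differences and will hold the patient variables, but the only variables it assigns to the outcome comparison are two characteristics of the GP. GP age is at best an indirect marker of patient age, and GP circle an indirect marker of local circumstances. Neither addresses differences in cancer, dementia or social position between GPs of similar age in the same circle.

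At stake is whether a difference in hospital deaths can be read as an effect of the care pathway. Naming the covariates before outcome data are seen also avoids a choice made after the fact.

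**Working it through.** **1. What is assigned to the outcome comparison**

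| Variable | Level | Stated role (Analysis section) |
|---|---|---|
| GP age category (5 years) | GP | Matching, else independent variable |
| GP circle | GP | Matching, else independent variable |
| Age category, gender, month of death | Patient | Describe GPs' populations |
| Cancer/non-cancer, dementia | Patient | Describe GPs' populations |
| Socio-economic status | Patient | Describe GPs' populations |

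No other section gives the patient variables a role in the outcome model. Table 4 promises distinctions by disease category in the consumption data, but names no model and does not cover age, gender or socio-economic status.

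**2. Whether adjustment is feasible**

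The linkage section says the IMA data reach the authors with a project code per patient and a pseudo code per doctor, so patient-level models with GPs as clusters are possible. Month of death is enough to place each death in its six-month phase.

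**3. Possible size of the bias**

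The plan has no figure of its own to reproduce here. It gives neither case-mix imbalances nor hospital-death rates by patient category, so both inputs are assumptions.

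Bias from one omitted characteristic = imbalance in its prevalence × difference in hospital death between its categories.

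| Imbalance | 10-point difference | 20-point difference | 30-point difference |
|---|---|---|---|
| 5 points | 0.5 | 1.0 | 1.5 |
| 10 points | 1.0 | 2.0 | 3.0 |

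Against the target of 50 % to 35 %, this is 0.5/15 = 3 % to 3/15 = 20 % of the effect, per characteristic. The sign is unknown, and several characteristics may add up or offset one another.

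**4. Effect on the false-positive rate**

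A two-sided 5 % test is assumed, since the article does not state alpha. If the study has exactly 80 % power for 15 points, the standard error is 15/(1.96 + 0.84) = 5.35 points. The false-positive rate with bias b is then P(Z > 1.96 − b/5.35) + P(Z < −1.96 − b/5.35):

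- b = 0.5: 5.1 %
- b = 2: 6.6 %
- b = 3: 8.7 %

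The more precise the comparison, the more a fixed bias matters. For a simple comparison of 180 with 180 GPs (equal groups assumed), 9 deaths each and an intra-class correlation of 0.2, the design effect is 1 + 8 × 0.2 = 2.6. The standard error is √(2 × 0.25 × 2.6/1620) = 2.83 points, and a 2-point bias gives about 10.9 %.

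**5. What adjustment does and does not remove**

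This was simulated for 180 versus 180 GPs with 9 deaths each, no true effect, a 10-point imbalance and a 20-point risk difference. The simulated spread between GPs corresponds to an intra-class correlation of about 0.03/0.25 = 0.12, below the plan's 0.2.

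| Scenario | Unadjusted estimate (false positives) | Adjusted estimate (false positives) |
|---|---|---|
| Measured case-mix only | −2.05 points (13.5 %) | −0.04 points (4.6 %) |
| Plus an assumed 5-point unmeasured volunteer effect | −6.92 points (79.8 %) | −4.92 points (53.3 %) |

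Patient-level adjustment removes the measured part and leaves the volunteer effect untouched.

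**The case against.** The strongest objection is that this is a short analysis section in an article and that the full covariate list may sit in a plan not shown. A reader might infer that the patient variables are barred from the models. The text does not say so: it says the data will also be available, and its explicit restriction to descriptive use applies to the survey and monitoring data. That stands. But the article is not silent on control variables. It names two, with a fallback, and gives the patient variables a different purpose.

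A second objection is that the analysis is longitudinal and every cluster has a usual-care phase. A within-GP before/after contrast would largely cancel stable differences in mix, so it would be too strong to say that such differences pass straight into the estimate. This stands as a possibility. However, the Analysis section describes participating versus non-participating populations and specifies no within-GP change. With 9 non-sudden deaths per GP per year, a six-month phase holds only four or five, so a GP's mix of deaths will also vary between phases.

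Three further inferences are tempting but unsupported:

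- That GP age was chosen for matching because it tracks patient age. The Analysis section gives no reason for the choice; the remark about GP age illustrates why an intra-class correlation is assumed.
- That adjustment would remove the confounding. It cannot reach the selection of GPs interested in palliative care, which may be the larger threat.
- That matching should be given up in favour of all non-participating GPs. The matching ratio is not stated, and the choice between the two is a trade-off that this point does not settle.

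**Conclusion.** The point holds in a limited form. In a non-randomised comparison, the stated control variables are GP age category and GP circle only, while patient variables to be supplied by the IMA are given a descriptive purpose. This sits badly with the plan's own expectation that GPs' patient populations differ. Neither the general mention of distinctions by disease category nor the unspecified longitudinal analysis closes the gap.

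The size is uncertain. The range of 0.5 to 3 points per characteristic rests wholly on the assumed imbalances and risk differences, with unknown direction. It is small to moderate beside a 15-point effect and would weigh more if the true effect were smaller. The change is worth making because it needs no new data, not because a large bias has been shown.

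**What to change.** State in the Analysis section that, whether or not GPs are matched, the primary and secondary outcome models will include as pre-specified patient-level covariates age category, gender, cancer/non-cancer, dementia and socio-economic status. Include phase, assigned from month of death, and keep GP age category and GP circle. The descriptive use of the patient variables can stay alongside.

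Add a limitation: adjustment reduces confounding from measured case-mix only, and differences arising because participating GPs were already interested in palliative care remain.

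The cost is a change of analysis wording, made before outcome data are examined. The variables are already listed as available from the IMA, so no new data collection is needed.
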